## Abstract

**Background:**

Previous clinical trials have demonstrated the potential efficacy of rechallenge with anti- epidermal growth factor receptor (EGFR) monoclonal antibodies (mAbs) for patients with *RAS*/*BRAF* V600E wild-type metastatic colorectal cancer (mCRC). Moreover, post hoc biomarker analyses of clinical trials has suggested that *RAS* status in circulating tumor DNA (ctDNA) has a high probability to select patients who could benefit from anti-EGFR mAb rechallenge.

**Methods:**

This trial is composed of 2 phases: a monitoring phase (REMARRY) and a trial phase (PURSUIT). A monitoring phase, the REMARRY study, aims to evaluate the dynamics of plasma *RAS* status during the subsequent treatments after refractory to anti-EGFR therapy in patients with mCRC with *RAS*/*BRAF* V600E wild-type tumors who have progressed after a response to previous anti-EGFR therapy, using a highly sensitive digital polymerase chain reaction OncoBEAM RAS CRC kit in a central laboratory (Sysmex, Japan). A trial phase, the PURSUIT trial, is a multicenter, single-arm phase II trial to assess the efficacy and safety of rechallenge therapy with panitumumab plus irinotecan in patients without *RAS* mutations in ctDNA (plasma *RAS* negative) in the REMARRY study. Key eligibility criteria of the PURSUIT trial include *RAS*/*BRAF* V600E wild-type mCRC in tumor tissue refractory or intolerant to fluoropyrimidine, oxaliplatin, and irinotecan; progression after complete or partial response to previous anti-EGFR therapy; plasma *RAS* negative (defined as plasma mutant allele frequencies [MAF] of all *RAS* ≤ 0.1%) within 28 days prior to enrollment; 4 months or more between the last administration of previous anti-EGFR mAb and the start of protocol treatment; and Eastern Cooperative Oncology Group (ECOG) Performance Status (PS) ≤ 1. The primary endpoint is the confirmed objective response rate (ORR). The target sample size of the PURSUIT trial is 50 patients. Biomarker analyses will be performed in parallel using the OncoBEAM RAS CRC kit and a next-generation sequencing-based ctDNA analysis (Guardant360).

**Discussion:**

Our trial aims to confirm the clinical benefit of anti-EGFR mAb rechallenge therapy in patients with plasma *RAS* negative. Moreover, through biomarker analyses, our trial will shed light on which patients would benefit from rechallenge in addition to being plasma *RAS* negative.

**Trial registration:**

The REMARRY study: UMIN, UMIN000036424. Registered date: April 5, 2019. The PURSUIT trial: jRCT, jRCTs031190096. Registered date: October 1, 2019.

## Background

Anti-epidermal growth factor receptor (EGFR), monoclonal antibodies (mAbs), panitumumab, and cetuximab are key standard drugs for patients with metastatic colorectal cancer (mCRC) with *RAS* wild-type tumors [1–4], achieving a median overall survival (OS) of approximately 30 months [1, 2, 5, 6]. Recently, the potential efficacy of rechallenge with anti-EGFR mAbs in a later setting for patients who had benefited from previous anti-EGFR mAb therapy has been suggested in retrospective and prospective studies [7–15]. The CRICKET trial, a single-arm phase II trial of rechallenge with cetuximab in 28 patients with a response to previous anti-EGFR mAbs, demonstrated a promising objective response rate (ORR) of 21% [11], whereas the Japanese phase II JACCRO-CC-08 and -09 trials showed limited efficacy of rechallenging anti-EGFR mAbs, with an ORR of 2.9–8.3% [13].

Plasma *RAS* status in circulating tumor DNA (ctDNA) is gaining attention as a novel predictive biomarker for the efficacy of rechallenging anti-EGFR mAbs. In the CRICKET trial, an enhanced ORR of 30% and longer progression-free survival (PFS) was observed in patients without *RAS* mutations in ctDNA just before the rechallenge [11]. Moreover, in a combined analysis of the JACCRO-CC-08 and -09 trials, negative for *RAS* mutations in ctDNA was associated with improved PFS and OS in rechallenge therapy with anti-EGFR mAbs [13]. Although post hoc analyses in clinical trials have indicated that plasma *RAS* status potentially predicts the efficacy of rechallenge therapy with anti-EGFR mAbs, the utility of liquid biopsy has not been prospectively validated. Furthermore, the appropriate mutant allele frequency (MAF) cut-off level in *RAS* mutations has not been established because a different cut-off had been adopted in each post hoc analysis.

This trial is designed to prospectively monitor plasma *RAS* status in patients experiencing initial response, followed by disease progression with prior chemotherapy containing anti-EGFR mAbs, and to evaluate the efficacy of rechallenge therapy with panitumumab plus irinotecan in patients negative for *RAS* mutations in ctDNA.

## Methods/design

### Overall trial design

This trial is composed of 2 phases: a monitoring phase (REMARRY) and a trial phase (PURSUIT). The overall trial design is shown in Fig. 1.

**Fig. 1 Fig1:**
[figure not shown]
Overall trial design. Liquid biopsies for OncoBEAM RAS CRC kit and/or Guardant360 will be performed in the PURSUIT trial at baseline, cycle 3, and after discontinuation of protocol treatment. C3: Cycle 3; G360: Guardant360; OncoBEAM: OncoBEAM RAS CRC kit; SOC: Standard of care. *Substitution of the result just before enrollment

### Monitoring phase (REMARRY)

The REMARRY study prospectively monitors plasma *RAS* status after refractory to anti-EGFR therapy in mCRC patients with *RAS*/*BRAF* V600E wild-type tumors in a tumor tissue sample who have progressed after a complete or partial response to previous anti-EGFR mAb therapy, which aims to evaluate the dynamics of plasma *RAS* status. Plasma *RAS* status is measured at disease progression during subsequent therapies, using a highly sensitive digital polymerase chain reaction (PCR) OncoBEAM RAS CRC kit in a central laboratory (Sysmex, Japan).

### Trial phase (PURSUIT)

The PURSUIT trial is a multicenter, single-arm phase II trial which assesses the efficacy and safety of rechallenge therapy with panitumumab plus irinotecan in patients with plasma *RAS* negative (defined as plasma MAF of all *RAS* ≤ 0.1%) in the REMARRY study.

#### Patient

Key eligibility criteria include *RAS*/*BRAF* V600E wild-type mCRC in tumor tissue refractory or intolerant to fluoropyrimidine, oxaliplatin, and irinotecan; progression after a complete or partial response to previous anti-EGFR mAb therapy; plasma *RAS* negative (MAF of all *RAS* ≤ 0.1%) within 28 days prior to enrollment; 4 months or more between the last administration of previous anti-EGFR mAbs and the start of protocol treatment; and Eastern Cooperative Oncology Group (ECOG) Performance Status (PS) ≤1. Details of the eligibility criteria are listed in Table 1.

**Table 1 Tab1:** Eligibility criteria for the PURSUIT trial

Inclusion criteria	Exclusion criteria
1. Unresectable colorectal cancer pathologically diagnosed as adenocarcinoma 2. *RAS* (*KRAS*/*NRAS*) and *BRAF* V600E wild-type in tumor tissue sample 3. Patients intolerant or refractory to chemotherapy, including fluoropyrimidine, oxaliplatin, and irinotecan 4. Complete or partial response to previous chemotherapy, including anti-EGFR mAb (cetuximab or panitumumab) according to RECIST version 1.1 5. Documentation of progression to previous anti-EGFR therapy within 2 months after last anti-EGFR mAb administration 6. Patients negative for *RAS* mutations in ctDNA using OncoBEAM RAS CRC kit within 28 days before enrollment in the REMARRY study 7. Four months or more between the last administration of previous anti-EGFR mAbs and the start of protocol treatment 8. Measurable disease according to RECIST version 1.1 9. ECOG PS 0 or 1 10. Age 20 years or older 11. Adequate major organ function assessed within 14 days before enrollment: a. Neutrophil count ≥1500/mm3 b. Platelet count ≥75,000/mm3 c. Hemoglobin ≥9.0 g/dL d. ALT and AST ≤100 IU/L (≤ 200 IU/L for patients with liver metastasis) e. Serum creatinine ≤1.5 mg/dL 12. Life expectancy of at least 12 weeks 13. Written informed consent obtained	1. Severe comorbidity. a. Synchronous active malignancies b. Uncontrolled brain metastasis or leptomeningeal metastasis c. Active infectious disease d. Uncontrolled ascites, pleural effusion, or pericardial effusion requiring continued drainage e. Uncontrolled diabetes mellitus or hypertension f. Myocardial infarction, severe/unstable angina pectoris, symptomatic congestive heart failure of New York Heart Association Class III or IV within 6 months before the enrollment g. Psychiatric diseases or psychiatric symptoms considered as difficult to enroll in a clinical trial 2. Underwent one of following treatments before protocol treatment: a. Extensive surgery within 4 weeks b. Colostomy/ileostomy within 2 weeks c. Chemotherapy within 2 weeks d. Radiation therapy within 2 weeks 3. CTCAE Grade ≥ 2 adverse events due to previous therapy, which are not recovered 4. History of severe infusion reactions to anti-EGFR mAbs 5. Intolerant to previous irinotecan therapy 6. Comorbidity or history of severe pulmonary disease 7. Men/women who are unwilling to avoid pregnancy; women who are pregnant or breastfeeding; women with a positive pregnancy test 8. Known active HCV or HIV infection 9. Any other patients who are regarded as inadequate for trial enrollment by investigators

*ALT* alanine aminotransferase, *AST* aspartate transaminase, *CTCAE* Common Terminology Criteria for Adverse Events, *ctDNA* circulating tumor DNA, *ECOG* Eastern Cooperative Oncology Group, *EGFR* epidermal growth factor receptor, *HCV* hepatitis C virus, *mAb* monoclonal antibody, *PS* Performance Status, *RECIST* Response Evaluation Criteria in Solid Tumors

#### Treatment

Patients will receive panitumumab 6 mg/kg plus irinotecan 150 mg/m^2^ biweekly until progressive disease, unacceptable toxicity, informed consent withdrawal, or patient’s death. The starting dose of irinotecan can be reduced to 120 mg/m^2^ or 100 mg/m^2^ according to adverse events during previous irinotecan therapy.

#### Outcomes and statistical considerations

The primary endpoint of the PURSUIT trial is the confirmed ORR, defined as the proportion of patients who achieve confirmation of complete or partial response by the investigator’s assessment with a minimum interval of 4 weeks. The secondary endpoints include PFS, time to treatment failure, duration of response, OS, disease control rate, and incidences of adverse events. Efficacy will be evaluated according to Response Evaluation Criteria in Solid Tumors (RECIST) version 1.1, using computed tomography at 6 and 12 weeks after the start of treatment and every 8 weeks thereafter. The ORR threshold is set at 10%, based on the results of previous clinical rechallenge trials with anti-EGFR mAbs [11, 13–15]. The required sample size was calculated as 45, with an ORR of 25% deemed promising (one-sided α, 0.05; β, 0.15) [11]. Considering drop-outs and ineligible patients, the target sample size is 50 patients. The primary endpoint will be analyzed in a full analysis set (PURSUIT-FAS) of all patients enrolled in the PURSUIT trial, receiving at least one dose of protocol treatment and satisfying all the inclusion and exclusion criteria. All statistical analyses will be performed using SAS software, version 9.2 (SAS Institute).

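### The sample size of 45 comes from an approximation; no responder cut-off at 45, or at the full 50, gives both one-sided α ≤ 0.05 and 85% power

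*Protocol article*

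**What the plan says.** All the design figures are in the protocol article, under Outcomes and statistical considerations.

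- Null rate: "The ORR threshold is set at 10%, based on the results of previous clinical rechallenge trials with anti-EGFR mAbs".
- Alternative, error rates and size: "The required sample size was calculated as 45, with an ORR of 25% deemed promising (one-sided α, 0.05; β, 0.15".
- Enrolment: "Considering drop-outs and ineligible patients, the target sample size is 50 patients". No drop-out rate is given; 50 × 0.9 = 45, so the allowance equals 10%.
- Analysis set: the confirmed ORR is analysed in PURSUIT-FAS, meaning enrolled patients "receiving at least one dose of protocol treatment and satisfying all the inclusion and exclusion criteria". The analysed number can therefore be below 50.

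The article gives no responder cut-off and describes no interim analysis.

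**The concern.** The primary endpoint is a count of responders in one arm, so any sensible success rule amounts to requiring at least r responders out of n. With n near 45 and a null rate of 10%, moving r by one changes both error rates in large steps. A large-sample formula ignores those steps, so the pair of error rates put into it need not be available from any actual rule at the resulting n.

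Two things are at stake. The stated β of 0.15 may not describe the design that will be run. And the go/no-go call for an observed ORR near 18% (8 of 45 or 9 of 50) sits exactly where neighbouring cut-offs fall on either side of the 5% limit.

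**Working it through.** **Inputs** (all from Outcomes and statistical considerations): p0 = 0.10, p1 = 0.25, one-sided α = 0.05, β = 0.15, required n = 45, target n = 50.

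**Step 1: reproduce 45.** Arcsine formula for one proportion:

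n = [(z₀.₉₅ + z₀.₈₅) / (2(asin√p1 − asin√p0))]²

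- z₀.₉₅ + z₀.₈₅ = 1.6449 + 1.0364 = 2.6813
- asin√0.25 − asin√0.10 = 0.5236 − 0.3218 = 0.2018; doubled, 0.4037
- n = (2.6813 / 0.4037)² = 44.1, rounded up to **45**

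The stated figure is reproduced. Approximate power at 45 by this formula is 85.6%. Other one-sided methods give 40 (score, 39.46), 46 (continuity-corrected, 45.88) and 47 (smallest n meeting both limits by exact binomial search).

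**Step 2: true error rates of each cut-off.** For the rule X ≥ r,

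P(X ≥ r) = Σ (k = r to n) C(n,k) pᵏ (1−p)ⁿ⁻ᵏ,

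evaluated at p = 0.10 for α and at p = 0.25 for power. These are the true operating characteristics of the cut-off, whichever test led to it.

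| n | Cut-off | α | Power | Both limits met? |
|---|---|---|---|---|
| 45 | ≥ 9 | 0.0320 | 82.7% | No, power short |
| 45 | ≥ 8 | 0.0757 | 90.6% | No, α too high |
| 50 | ≥ 10 | 0.0245 | 83.6% | No, power short |
| 50 | ≥ 9 | 0.0579 | 90.8% | No, α too high |

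A higher cut-off lowers power further and a lower one raises α further, so no other r helps. True β is 1 − 0.8275 = 0.173 at 45 and 1 − 0.8363 = 0.164 at 50.

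**Step 3: every analysed size from 45 to 50**, using the lowest cut-off that keeps α ≤ 0.05:

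| FAS size | Cut-off | α | Power |
|---|---|---|---|
| 45 | ≥ 9 | 0.0320 | 82.7% |
| 46 | ≥ 9 | 0.0364 | 84.7% |
| 47 | ≥ 9 | 0.0411 | 86.5% |
| 48 | ≥ 9 | 0.0463 | 88.1% |
| 49 | ≥ 10 | 0.0215 | 81.7% |
| 50 | ≥ 10 | 0.0245 | 83.6% |

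Only 47 and 48 meet both limits. Power falls between 48 and 49 because the cut-off moves from 9 to 10. From 51 (≥ 10: α 0.0279, power 85.4%) every size checked, up to 65, meets both. The boundary is ≥ 9 for n = 42–48 and ≥ 10 for n = 49–56.

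**Step 4: what common tests would do at the two disputed counts** (critical value 1.645).

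- 8 of 45: the score test gives (0.1778 − 0.10)/√(0.09/45) = 1.739 and rejects. The arcsine test gives 1.523 and does not. The continuity-corrected test gives (8 − 0.5 − 4.5)/√(45 × 0.09) = 1.49 and does not. The Wald test gives 0.0778/√(0.1778 × 0.8222/45) = 1.36 and does not.
- 9 of 50: the score test (1.886) rejects. The arcsine test (1.646) rejects by about 0.001. The Wald test, 0.08/√(0.18 × 0.82/50) = 1.47, does not reject. The exact test does not reject, since P(X ≥ 9) = 0.0579.

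**The case against.** The strongest reply is that 45 is a correct result from a recognised formula. The article reports inputs to a sample-size calculation and does not claim exact operating characteristics; that a discrete count misses nominal rates is a general feature of single-arm binomial designs. This stands as far as it goes: a reader might infer an arithmetic error, and Step 1 shows there is none. It does not remove the point, because the stated α and β are what readers will take as the design's properties, and no rule at 45 has them.

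Second, 50 is an enrolment target and not the planned analysis number, and an analysis set of 47 or 48 meets both limits. This also stands. The figures for 50 apply only if every enrolled patient is treated and eligible.

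Third, a condensed article normally leaves the test and the cut-off to the full protocol or SAP, which are not shown. That is accepted: their absence here is not part of the point. No later choice of test, however, can make the stated pair attainable at 45 or 50.

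A reader might also infer that any normal-approximation test would push type I error above 5%. The documents do not support that. They name no test, and Step 4 shows that the result depends on both test and n. At 45 only the uncorrected score test rejects at 8 responders; the arcsine method that reproduces 45 needs 9 and has true α 0.032. Type I error can be kept at or below 0.05 at every n.

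**Conclusion.** The point holds in a limited form. For 10% versus 25%, the stated one-sided α of 0.05 and β of 0.15 cannot both be met at 45, or at 50 if all patients are analysed. With α held, power is 82.7% at 45 (2.3 points short) and 83.6% at 50 (1.4 points short). Over analysis sets of 45 to 50 it ranges from 81.7% at 49 to 88.1% at 48.

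This rests on a single-stage design with independent responses and a success rule based on the responder count in PURSUIT-FAS. It does not rest on which test is used.

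The shortfall is minor and does not threaten the trial. It might suggest raising the required number to 47 under an unchanged target of 50, but that would not secure 85%: analysis sets of 49 and 50 still give 81.7% and 83.6%.

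**What to change.** Keep the enrolment target of 50 and make two changes to the text.

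1. Restate the power as about 83%: exact 82.7% at 45 and 83.6% at 50, with a range of 81.7% to 88.1% over analysis sets of 45 to 50. Say that 45 is consistent with an arcsine approximation, if the sponsor confirms that this was the method.
2. Base the success call on the exact binomial boundary against 10%: at least 9 responders if PURSUIT-FAS has 42–48 patients, at least 10 if it has 49–56. True one-sided α then stays at or below 0.05 whatever the final analysed number. If the full protocol or SAP already fixes this boundary, only the first change is needed.

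The cost is two sentences and a slightly less favourable stated power. No patients, visits or assessments are added.

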#### Biomarker analysis

Liquid biopsies will be performed in the PURSUIT trial at baseline, cycle 3, and after discontinuation of protocol treatment. The ctDNA will be analyzed using a highly sensitive digital PCR method, OncoBEAM RAS CRC kit, and a targeted next-generation sequencing, Guardant360. Figure 1 shows at which point each analysis is performed. OncoBEAM RAS CRC kit, which uses beads, emulsion, amplification, magnetics (BEAMing) digital PCR technology, detects 34 mutations in *KRAS*/*NRAS* codons 12, 13, 59, 61, 117, and 146 in plasma [16]. This test is an in vitro diagnostic test, CE-marked in Europe and approved by the Pharmaceuticals and Medical Devices Agency in Japan to detect *RAS* mutations in ctDNA derived from mCRC. Several prospective and retrospective studies comparing *RAS* status as determined by BEAMing in plasma and the tissue reference method have reported high concordance rates, from 86.4 to 93.3% [17–20]. Guardant360 is a hybrid capture-based next-generation sequencing panel of ctDNA by Guardant Health, which is a Clinical Laboratory Improvement Amendments-certified, College of American Pathologists-accredited, New York State Department of Health-approved laboratory, as previously described [21]. Briefly, Guardant360 detects 74 gene alterations, including single nucleotide variants, indels, amplifications, and fusions, with a reportable range of ≥0.04, ≥0.02, ≥0.04%, and ≥ 2.12 copies, respectively.

### Integrated analysis

Data on baseline characteristics and clinical outcomes will be collected on patients enrolled in the REMARRY study receiving rechallenge with anti-EGFR mAb in clinical practice from the PURSUIT trial (clinical practice set [plasma MAF of all *RAS* > 0.1%]). An integrated analysis, including PURSUIT-FAS (MAF ≤0.1%) and the clinical practice set (MAF > 0.1%), will be performed to determine a clinically significant plasma *RAS* MAF cut-off value.

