## Discussion

Post hoc analyses of clinical trials have indicated the clinical significance of plasma *RAS* status at baseline as a predictive biomarker for the efficacy of rechallenge with anti-EGFR mAbs in patients with mCRC. Beyond these data, our trial will reveal some important points to select patients who benefit from rechallenge with anti-EGFR mAbs.

First, our trial’s findings will enable us to estimate the optimal cut-off value for *RAS* MAF in ctDNA associated with the efficacy of rechallenge with anti-EGFR mAbs. Given the cut-off values have varied in previous reports, the optimal value remains unclear. Although the absolute cut-off value is defined as 0.1% in the PURSUIT trial based on the previous retrospective or *post-hoc* analyses [14, 23], integrated analysis of rechallenge with anti-EGFR mAbs in PURSUIT-FAS (MAF ≤0.1%) and the clinical practice set (MAF > 0.1%) will be performed to determine the optimal cut-off value of plasma *RAS*.

Second, our trial could shed more light on the relationship of temporal-spatial tumor heterogeneity and rechallenge efficacy. Previous reports have focused mainly on plasma *RAS* status just before rechallenge; the role of plasma *RAS* status just after refractory to previous anti-EGFR therapy as a biomarker for rechallenge remains unknown. Moreover, it is unclear whether acquired alterations other than *RAS* mutations, including *BRAF*, *EGFR*, *HER2, MET*, and *PIK3CA,* affect the efficacy of rechallenge with anti-EGFR mAbs [24–28]. Our trial monitors serial ctDNA status from just after refractory to the previous anti-EGFR therapy using OncoBEAM RAS CRC kit and a plasma-targeted next-generation sequencing panel (Guardant360), allowing us to reveal how the dynamics of *RAS* mutations and other acquired alterations influence rechallenge efficacy.

Third, our trial could also clarify the significance of clinical factors in a plasma *RAS*-negative population. Although clinical factors, including the anti-EGFR mAb-free interval and PFS for previous anti-EGFR therapy, have been assessed in patients without a plasma *RAS* test, it is unknown whether clinical factors still predict the efficacy of rechallenge with anti-EGFR mAbs in patients with plasma *RAS* negative. Our trial will help patient selection by using clinical factors and molecular markers to enhance the efficacy of rechallenge with anti-EGFR mAbs in patients with mCRC.

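### The pooled cut-off analysis cannot tell MAF above 0.1% apart from treatment outside the trial, because its two sets divide exactly at 0.1%

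*Protocol article*

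**What the plan says.** The Integrated analysis section of the protocol article pools two sets. The low-MAF set is PURSUIT-FAS, that is, trial patients "receiving at least one dose of protocol treatment and satisfying all the inclusion and exclusion criteria". They receive the protocol combination of panitumumab and irinotecan. Confirmed response is judged by RECIST 1.1, "using computed tomography at 6 and 12 weeks after the start of treatment and every 8 weeks thereafter".

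The high-MAF set consists of "patients enrolled in the REMARRY study receiving rechallenge with anti-EGFR mAb in clinical practice". The sentence that defines it is loosely worded where it relates these patients to PURSUIT, but both the Integrated analysis section and the Discussion label the set as MAF above 0.1%.

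The purpose appears twice. The Integrated analysis section says "An integrated analysis, including PURSUIT-FAS (MAF ≤0.1%) and the clinical practice set (MAF > 0.1%), will be performed to determine" a cut-off. The Discussion makes this the first of three expected contributions: pooling the same two sets "will be performed to determine the optimal cut-off value of plasma" RAS. The Discussion also says that 0.1% was taken from earlier retrospective or post hoc work and that the best value is still unclear.

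**The concern.** The analysis is meant to find the MAF level at which rechallenge stops working, and 0.1% is the first candidate because it is the trial's entry rule. Yet no patient above 0.1% is observed under trial conditions, and none at or below 0.1% under practice conditions. Any difference in outcome that comes from regimen, selection for the trial or the way response is assessed will look like a step at exactly 0.1%.

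The search is thus drawn towards the threshold already used for enrolment. A reader could take the result as confirmation of that threshold, and it could then be used to decide who is considered for rechallenge. This follows from the stated set definitions, so an analysis plan that is not shown could not repair it by modelling while those definitions stand.

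**Working it through.** **Structure (no assumptions needed).** Let S = 1 for the practice set and M = 1 for MAF above 0.1%. By the definitions in the Integrated analysis section, S = M for every patient. In

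logit P(response) = b0 + b1·S + b2·M + covariates

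only the sum b1 + b2 can be estimated. The matrix (intercept, S, M) has three columns and rank 2 at any sample size. Adjusting for a measured factor such as performance status may remove the part of the difference which that factor carries, but it does not divide the remainder between b1 and b2.

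**Inputs for size.** The document gives no figure for the integrated analysis, so there is none to reproduce.
- Trial patients: 45, the required number in Outcomes and statistical considerations. The arcsine formula reproduces it: [(1.645 + 1.036) / (2 × (0.5236 − 0.3218))]² = 44.1, rounded up to 45.
- Trial ORR: 25%, the value called promising in that section.
- Practice patients: 20, 30 or 50 (assumed; not stated).
- Practice ORR: 25, 20, 15 or 10% (assumed).
- MAF: 80% of trial patients at zero and the rest spread over 0.01–0.1%; practice log-uniform over 0.1–20% (assumed).
- True MAF effect: none.

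**Test at 0.1%.** With ℓ(k,n) = k·ln(k/n) + (n−k)·ln(1−k/n),

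LR = 2[ℓ(a,45) + ℓ(b,m) − ℓ(a+b,45+m)],

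where a and b are the responders and m is the number of practice patients. The split counts as nominally significant if LR > 3.84 and the trial ORR is the higher. Example with m = 30 and a = 11: b = 2 gives 2(−25.027 − 7.348 + 34.585) = 4.42, significant; b = 3 gives 2(−25.027 − 9.752 + 36.102) = 2.64, not significant.

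The groups at 0.1% are simply the two sources, so this test does not depend on the assumed MAF distribution. Its probability can also be found exactly by summing the two binomials over all (a, b). The last column does depend on the MAF distribution. It shows how often 0.1% has the best LR among 0.02, 0.05, 0.1, 0.2, 0.5, 1, 2 and 5%.

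| ORR trial vs practice | Significant at 0.1%, simulated (4,000 runs) | Exact, m = 20 / 30 / 50 | 0.1% chosen as best |
|---|---|---|---|
| 25% vs 25% | about 3% | 2.7 / 2.9 / 2.6% | 8–11% |
| 25% vs 20% | 6–9% | 6.8 / 8.1 / 8.9% | 13–14% |
| 25% vs 15% | 16–23% | 15.5 / 19.6 / 24.3% | 20–21% |
| 25% vs 10% | 31–51% | 32.2 / 41.0 / 52.0% | 29–30% |

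The simulated and exact figures agree to within about one percentage point.

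**Other cut-offs.** Take m = 30 and ORR 25% vs 10%, again with no MAF effect.
- At 1%, the log-uniform assumption puts about 13 practice patients at or below the cut and 17 above. The pooled low group expects (45 × 0.25 + 13 × 0.10)/58 = 21.6% and the high group 10%, an apparent gap of 11.6 points.
- At 0.05%, about 5 trial patients lie above the cut. The low group expects 25% and the high group (5 × 0.25 + 30 × 0.10)/35 = 12.1%, a gap of 12.9 points.
- At 0.1% the gap is the full 15 points.
- Within practice alone at 1%, or within the trial alone at 0.05%, the expected gap is zero, which is correct.

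Pooling therefore carries part of the source effect to every cut-off, while a within-source contrast does not.

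**The case against.** **Cut-offs other than 0.1%.** A reader might infer that the analysis can say nothing about any cut-off. That goes too far. A cut above 0.1% divides the practice set and a cut below it divides PURSUIT-FAS, so both can be studied free of source. Exact collinearity concerns the indicator at 0.1%, not MAF as a continuous measure, and the article does not commit itself to a pooled search over indicators. This stands and limits the point. Within-source work still cannot test 0.1% itself, because neither set spans it.

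**How different the sources are.** The article is a condensed account. That it names no regimen, eligibility rule or scan schedule for the practice set does not show that the full protocol lacks them. What it does state brings the sets closer: both come from REMARRY, with wild-type tissue, an earlier response and later progression, and the same central plasma assay. Baseline characteristics are collected in the practice set. This stands too. The documented fault is the composition of the sets, and it would remain even if practice data were collected carefully.

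**Size.** A practice ORR of 5% against 25% in the trial gives 61–84% nominal significance, and it is tempting to quote that. Nothing in the document supports a source effect so large. Nor does it say that response is the outcome to be used: it speaks only of clinical outcomes, and overall survival, for example, would not depend on the scan schedule.

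**Importance.** The integrated analysis is neither the primary nor a listed secondary endpoint of PURSUIT. That is correct.

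**Conclusion.** The point holds in a bounded form. At 0.1%, data source and MAF group are the same variable, and no adjustment can separate them. This conclusion rests only on the stated set definitions. At other cut-offs, pooled estimates are partly confounded but within-source estimates are not.

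The percentages are illustrations. They rest on assumed practice-set sizes, response as the outcome and an assumed source effect, and they range from close to the background rate of about 3% (6–9% at ORR 25% vs 20%) to 31–51% (25% vs 10%). They show that a modest source difference can produce an apparent cut-off at 0.1%; they do not show that it will.

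A reader might also infer that the trial's main conclusion is at risk. It is not: confirmed ORR, the 10% and 25% hypotheses and the sample size do not use the practice set. What is at risk is the claim to determine an optimal cut-off, and above all any claim that the pooled data validate 0.1%. This should be fixed, but it is not critical to the primary result.

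**What to change.** 1. Define the clinical practice set as all REMARRY patients rechallenged outside PURSUIT, whatever their MAF, with the same data collected, so that the sources can overlap at or below 0.1%.
2. Report the relation between MAF and outcome within each source. If overlap exists, add a pooled model with a source term and few other covariates: at ORR 25% and 10% there would be only about 45 × 0.25 + 20 × 0.10 = 13 to 45 × 0.25 + 50 × 0.10 = 16 responders. Use a MAF scale that can handle zero values, since a plain logarithm cannot, and give a bootstrap interval for any cut-off.
3. Use the practice patients who meet the other PURSUIT criteria only as a sensitivity analysis. Plasma-negative patients treated outside an open trial may often be those who fail its criteria, so a strict filter could remove the overlap.
4. If no practice patients at or below 0.1% accrue, replace the aim of determining a cut-off with an exploratory one, confine the search to within source, and do not present 0.1% as validated by the pooled data.

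The cost is revised wording, added data collection for a number of patients that the document does not allow one to estimate, and a less definite statement about the cut-off.
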